### 9.2.2 Safety analysis

Calculation of the proportion of subjects with AEs and SAE by treatment group, type of AE, gender, severity and relationship to study drug (see section 8.1).

### 9.2.3 Analysis populations

Two populations will be analyzed for efficacy:

Per protocol population: includes all subjects who were received the full treatment course they were randomized to and have a final efficacy assessment. .

Intent to treat population: includes all subjects who received at least one dose of study drug and have a final efficacy assessment.

All subjects who received at least one dose of study drug will be included in the safety analysis.

### 9.2.4 Interim Analysis

No interim analysis is planned.

### 9.2.5 Reasons for discontinuation of treatment/study

For subjects who have provided reasons for discontinuation of participation in study treatments or the whole study or for their not attending all scheduled treatment days, the reasons will be categorized into four groups:

- reasons related to drug administration,
- reasons related to study drug procedures, but not drug administration,
- other reasons,
- no reason provided

and the proportion of subjects in each category will be calculated by number of treatments prior to withdrawal.

This analysis can serve as input into the design of a follow up study (if the present study provides proof of concept) which needs to include addressing how a multiple dose albendazole regimen can be implemented for community treatment in a way that maximizes compliance. Compliance will be critical to achieving reliable reduction of *Loa loa* microfilaraemia below the risk level in the total population to be treated subsequently with ivermectin.

## 10 PROBLEMS ANTICIPATED

Problems anticipated and contingency plans:

- Prevalence of *L. loa* in the study area and/or percentage of subjects eligible and willing to participate in the study too low to recruit the target number of subjects. This will necessitate screening a larger number of subjects to achieve the necessary number of subjects.
- The number of subjects with high microfilaria levels (>30000) tends to be low, even in areas with high prevalence of *Loa loa*. Since subjects with this level of *Loa loa* microfilaraemia are those most likely to experience signs and symptoms and potential long term sequelae of loiasis and are at high risk for SAE in case of ivermectin treatment, they are of particular interest in this study. If after final subject qualification the number of subjects with >30000 mf/ml is lower than 15, measures for recruitment of subjects with high microfilaria levels will be discussed with the sponsor.

## 11 ETHICS

### 11.1 Informed consent

The method for obtaining informed consent is described in section 6.1.3.2. The informed consent information is provided in the Attachment.

### 11.2 Gender related issues

Ideally, 50% of the subjects in each microfilaria strata would be women. However, because of (1) pregnancy being an exclusion criterion and (2) prevalence and intensity of infection tending to be lower in females than males, it is unlikely that this will be achieved. There is currently no reason to suspect that the host gender affects the response of the parasite to albendazole.

### 11.3 Potential risks to subjects

No experimental procedure is being used in this study. The protocol procedures the subjects will undergo include a finger prick (to obtain samples for the parasitological examinations at screening, prior to each treatment and at the additional efficacy follow up visits) and a venous blood sample (4ml ) for determination of ALT, AST, creatinine and haemoglobin levels and a CBC at the screening visit (see section 6.1.3). The risks associated with these procedures are minimal.

Subjects will be treated with albendazole which is being used in Cameroon and other countries for treatment of intestinal worms and has been proven to be safe for mass treatment of lymphatic filariasis without medical supervision (Horton et al., 2000; Ismail et al., 2001). During the previous trials with albendazole in subjects with loiasis, there were either no clinical adverse effects and no observed hepatotoxicity, renal toxicity, or hematologic abnormalities attributable to the drug (Klion *et al.*, 1993) or adverse events were not severe, transient and/or observed with similar frequency in the placebo group (see section 3).

### 11.4 Potential benefits to subjects

Subjects who participate in the preliminary survey as well as in final subject selection will benefit from having their health status evaluated and either treated immediately, or being referred to a hospital/treatment center for treatment of illnesses that go beyond the treatment capability of the study team in the village.

Any subject who qualifies for and participates in the study will benefit from having clinical examinations and treatment of minor illnesses as part of the study, or referral to the next health center for illnesses outside the scope of village-based treatment during this study every two months.

The prevalence of intestinal helminths, in particular hookworm (Ratard et al, 1992), in the study area is low with less than 15% of adults estimated to be infected. Thus, only the rare subject who participates in the study and has intestinal helminths not accompanied by signs and symptoms (e.g. diarrhoea, abdominal pain, vomiting) and is randomized to one of the two albendazole treatment groups could benefit from the effect of albendazole on their intestinal helminths. Given that albendazole is a very safe treatment, this potential benefit will be extended to subjects who received only placebo during the study by offering them albendazole treatment after completion of the study and unblinding.

If one or both of the albendazole treatment regimens result in reduction of *L.loa* microfilaremia, those subjects in which this reduction occurs will benefit from this.

Since this is a small proof-of-concept study, expansion of a treatment regimen for which the benefit has not yet been definitively established to all study participants or the community from which they are coming is premature.

### **11.5 Potential benefits to communities**

Communities with loiasis would benefit from the development of a safe and effective treatment reducing LLM, because there is currently no safe treatment for to reduce LLM and physicians are thus not able to offer treatment to *Loa loa* infected subjects who asked for that type of treatment.

Among communities with loiasis, those co-endemic for onchocerciasis and/or lymphatic filariasis would benefit additionally from a mass treatment suitable *Loa loa* treatment through the reduced risk of SAEs during CDTI and/or implementation of lymphatic filariasis control.

### **11.6 Inclusion of a placebo arm**

As outlined in section 3, inclusion of a placebo group is necessary to be able to assess whether any reduction of microfilaremia counts in either of the two albendazole treatment arms is statistically significantly associated with the use of albendazole and thus likely to reflect more than the natural longitudinal variation of LLM as seen in the placebo group.

### **11.7 Data safety monitoring**

Given albendazole's excellent safety record in the treatment of intestinal helminths and in lymphatic filariasis control programs, a data safety monitoring board is not required.

### **11.8 Information of the communities of the study results**

Once the final data from the study are available and have been discussed with the stake holders, each community will be visited to inform them about the results and what will be done in consequence of the results obtained.

### **11.9 Subject Compensation**

Subjects included in this trial will be compensated for any expenses incurred during the transport to the study site but will not have direct financial compensation for study participation. Information on indirect compensation via the treatment of minor complaints detected during the clinical examinations is provided in section 11.4.

### **11.10 Insurance**

A clinical trial insurance will be taken out through TDR.

## **12 OBLIGATIONS OF THE INVESTIGATOR**

The principal investigator will ensure that the study will be conducted in accordance with the ethical principles that have their origin in the Declaration of Helsinki (as amended, October 2000) and that are consistent with good clinical practice (GCP) and the Standard Operating Procedures for Clinical Investigators (TDR/TDP/SOP/99.1).

### **12.1 Ethics Committee Approval**

The protocol and the informed consent form will be approved by the Ethics Committee of the Cameroon Health Service and the WHO prior to initiation of the study.

## 12.2 Pre study Documentation

The principal investigator will provide the sponsor with the following documents:

- A copy of the National Ethics Committee (NEC) approval letter for the protocol and informed consent. Any changes in this study or unanticipated problems involving risks to the subjects will be reported promptly to the NEC and the TDR Product Manager.
- Current signed and dated curricula vitae for the investigators
- Copy of the approved informed consent documents to be used.
- Copy of the protocol sign-off page signed by the investigators.

Subject screening will not be initiated until clearance has been received from the National Ethics Committee and the WHO Ethics Review Committee.

## 12.3 Study management

The principal investigator is responsible for assigning the responsibilities to each study team member and to ensure that they fulfill their responsibilities.

The study team will consist of:

- One medical doctor who will assist the principal investigator in examining the patients.
- Two Laboratory technicians who will be responsible for collecting blood samples for CBS and laboratory evaluations.
- One nurse who will measure blood pressure and body temperature as needed.
- One secretary who will register patients during the preliminary survey, and who will also help in registering data.
- One local person in each village who will assist the principal investigator in the sensitization of patients and help participants to liaise with the PI during the course of the study between visits to the villages.
- One district medical officer.

## 12.4 Informed Consent

Informed consent will be obtained prior to any study related procedures (see attached).

## 12.5 Serious Adverse Event Reporting

The principal investigator agrees to report all SAEs to GSK and the National Cameroonian authority, as per their requirements and described in section 8.6.

|                                                                   |               |                        |
|-------------------------------------------------------------------|---------------|------------------------|
| GSK Global Clinical Safety & Pharmacovigilance (GCSP): | FAX    | [name] |
|                                                                   | PHONE: | [name] |

The principal investigator is responsible for ensuring that any sub-investigator promptly brings SAEs to the attention of the investigator.

## 12.6 Source Records

The principal investigator is responsible for recording of all relevant data in the source records and their correct transcription to the CRF.

The principal investigator agrees that qualified representatives of the sponsor and the national authority have the right, both during and after this study, to direct access to the source documents.

## 12.7 Protocol Amendment

Once the study has started, the investigator will adhere to the protocol and ensure that it is strictly followed. Deviations to protocol procedure(s) that involve the subjects will not be made without the agreement of the sponsor except when necessary to avoid immediate danger to a trial subject.

Proposed changes will be discussed with the TDR Product Manager. If the TDR Product Manager agrees to the changes, they will be outlined as a protocol amendment along the lines indicated in the TDR SOP for Clinical Investigators. The document will be signed by the investigator and TDR Product Manager and appended to the original protocol.

Any such modification of the protocol that has an impact on the risk and benefits of the study participants will require a submission to the National EC and the WHO ERC prior to implementation.

In the case of minor modifications that do not have impact on the risk-benefit of the subjects during participation in the trial, or which only impact on administrative activities, the modification will be considered a simple notification that does not require Ethics Committee approval.

## 12.8 Quality Assurance

The principal investigator is responsible for ensuring that all members of the study team are trained on the requirements for conducting the study according to Good Clinical Practice and the applicable regulatory requirements.

The investigator will accordingly ensure that

- the data in the source records are accurate, complete and legible,
- transcribed accurately to the Case Report Forms
- entered accurately into the data base and analysed as planned in the protocol.

Adherence to GCP, consistency of the data in the source records with those on the CRF and drug accountability will be monitored by a TDR clinical monitor.

## 12.9 Interim Report

11 months after the initiation of the study the investigator will provide an interim report including a summary of number of subjects enrolled by microfilaria strata, summary statistics of microfilaria counts pre-treatment and at each follow up time point completed up to 1 month prior to the date of the report (range, median, Williams geometric means for each microfilaria stratum), adverse events (number of adverse events by type, severity, seriousness separately for each microfilaria stratum).

The same type of report will be generated 23 months after the initiation of the study unless at that time the study has been completed and a final study report (see section 12.10) has or will shortly be provided within the next 2 months.

## 12.10 Final Study Report

The clinical investigator will complete a report notifying the sponsor and the national authorities, if required, of the conclusion of the study within 2 weeks of the last follow up visit. A final report including all data analyses and conclusions will be sent to the TDR Product Manager within 3 months of the last follow up visit.

### **12.11 Record retention**

The investigator will retain all study related records until 5 years after the publication of the results unless otherwise notified by the sponsor.

### **12.12 Change in Investigator(s)**

If the principal investigator retires, relocates, or otherwise withdraws from conducting the study, the responsibility for maintaining records will be transferred to another investigator with the same qualifications. The sponsor and the National Ethics Committee will be notified of the change.

### **12.13 Confidentiality**

All unpublished information that the sponsor gives to the investigators will be kept confidential and shall not be published or disclosed except to study personnel under the supervision of the investigator, Ethical Committees, or duly authorized representatives of regulatory agencies, under the condition that they maintain confidentiality. The investigator will not make a patent application based on the results of this study and will not assist any third party in making such an application without the written authorization of the sponsor, unless otherwise specified in the TSA.

## **13 TERMINATION OF THE STUDY**

### **13.1 Termination by the Sponsor**

The sponsor may terminate the study at any time for any of the following reasons:

1. Failure to enroll subjects.
2. Protocol violations.
3. Unsafe or unethical practices.
4. Administrative decision.

### **13.2 Termination by the Investigator**

If the investigator terminates the study prematurely, the investigator will provide a written statement to the sponsor and the National EC describing why the study was terminated prematurely. The investigator will generate a report of the data obtained until the date of study termination.

## **14 QUALITY ASSURANCE**

See section 12.8.

## **15 PUBLICATIONS**

The investigators will target publication of the results in a recognized (refereed) scientific journal. The investigators will submit publications, reports, abstracts, manuscripts and/or other presentation materials to the sponsor for review prior to submission for publication or presentation. The sponsor shall have 60 calendar days to respond with any requested revisions, including without limitation, the deletion of confidential information. The investigators will act in good faith upon such requested revisions, except the investigators will delete any confidential information from such proposed publication or presentation.

## **17 ATTACHMENTS**

Informed Consent Information for Initial Screening (preliminary survey)

Informed Consent Information for final subject qualification and study participation

SAE Reporting Form

SAE Form (Section 12, for follow up information)

Pregnancy Notification Form

Pregnancy Follow-Up Form - Current Pregnancy Information

## **Protocol Amendment**

### **Efficacy of albendazole in decreasing *Loa loa* microfilaraemia**

The protocol of the study on the Efficacy of albendazole in decreasing *Loa loa* microfilaraemia started in March 2007 in the south Province of Cameroon. This study which was a double blind study had to continue until 18 month (September 2008). The study continued to this term and the blind was lifted. Due to tendency of decrease in one of the group, it was proposed that the follow-up should continue to 24 months with two supplementary control of the *Loa loa* microfilaremia at M21 and M24.

The procedure of blood sampling will remain as from M0 to M24. The blood sample will be collected almost and the same time, with the same material and with the same precautions. The examination of slides will follow the same procedures as the previous examinations.

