## 5.2 Primary endpoint

The primary endpoint will be the proportion of subjects in whom there is a sustainable ( $\geq 4$  months) reduction in microfilaremia by  $\geq 50\%$  of pretreatment values at any time point post the first drug administration by treatment group.

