#### 7.1.1 Primary

The primary efficacy variable is the proportion of subjects in each treatment group whose microfilaria count has been sustainably reduced by 50% from the baseline value at any time point after the first dose. A sustainable reduction by 50% is defined as a reduction to 50% of baseline LLM for at least 4 months.

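### M21 and M24 were added after unblinding because one arm was falling, and nothing in the amended protocol fixes the primary analysis or its populations at M18

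*Protocol*

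**What the plan says.** **Timing and reason.** The Protocol Amendment states: "The study continued to this term and the blind was lifted". It then gives the reason for continuing: "Due to tendency of decrease in one of the group, it was proposed that the follow-up should continue to 24 months". The addition is "two supplementary control of the *Loa loa* microfilaremia at M21 and M24". Subjects are to sign a further consent for the prolongation, and during that explanation each is told how their own microfilaremia (LLM) has been moving.

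**Endpoint.** Section 5.2 counts a sustained reduction "at any time point post the first drug administration by treatment group". Section 7.1.1 repeats this as "sustainably reduced by 50% from the baseline value at any time point after the first dose" and adds: "A sustainable reduction by 50% is defined as a reduction to 50% of baseline LLM for at least 4 months". Neither section names a last visit. The sustained reduction below 8100 mf/ml (sections 5.3 and 7.1.2) has no last visit either.

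**Visits and populations.** Sections 6.1.7.1 and 7.2 list M2, M4, M6, M8, M10, M14 and M18. Section 9.2.3 admits a subject to the intent-to-treat or per-protocol population only with a final efficacy assessment, which it does not define.

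**Placebo subjects.** Section 11.4 extends a possible benefit to those who received only placebo "by offering them albendazole treatment after completion of the study and unblinding".

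**The concern.** In the protocol before amendment, the phrase about any time point was bounded in practice because M18 was the last visit. The amendment moves the last visit without restating the endpoint, the analysis populations or the analysis cut-off. The visits it adds were chosen with treatment codes open and because one arm was moving in a particular direction.

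Two things follow if M21 and M24 are allowed into the primary analysis. A subject who first reaches the 50% level at M18 and stays there through M24 becomes a responder who would not have been one at M18. And if the final efficacy assessment is read as M24, a subject with complete blinded data to M18 who declines the new consent leaves both efficacy populations. That decision is taken after unblinding and with knowledge of the subject's own trend.

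What is at stake is the meaning of the one randomised, blinded comparison the trial has, and the 0.025 level set for each of its two tests.

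**Working it through.** **1. The plan's own figure.** Section 9.1 gives 16 per arm for at least 90% power, with placebo response below 1/10^6, active response 50% and two-sided alpha 0.025. The usual pooled formula is

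n = [z(0.9875)·√(2·p̄·(1−p̄)) + z(0.90)·√(p0(1−p0)+p1(1−p1))]² / (p1−p0)²

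With p̄ = 0.25: [2.241·√0.375 + 1.282·√0.25]² / 0.25 ≈ 16.2, so 17 per arm; power at 16 is 89.5%. Exact power of the uncorrected chi-square at 16 is 96.2%. Dropout: 16/(1−0.20) = 20. The stated size reproduces and is not in dispute.

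**2. Response windows.** For each starting visit, take the shortest run of visits spanning at least 4 months.

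- To M18: 2-4-6, 4-6-8, 6-8-10, 8-10-14, 10-14, 14-18. Six windows.
- To M24: the same six plus 18-21-24. Seven windows. M18 to M21 and M21 to M24 are 3 months each, so neither qualifies alone.

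**3. How near one conversion can be to the boundary.** Uncorrected chi-square (section 9.2.1), 20 per arm, two-sided 0.025:

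| Placebo responders | Active responders, p | One more active responder, p |
|---|---|---|
| 0 | 4, p = 0.035 | 5, p = 0.017 |
| 1 | 6, p = 0.038 | 7, p = 0.018 |
| 2 | 8, p = 0.0285 | 9, p = 0.013 |

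For the first row: 40·(4·20)²/(20·20·4·36) = 4.44, p = 0.035; and 40·(5·20)²/(20·20·5·35) = 5.71, p = 0.017. Any discrete test has such a boundary, so this shows only that one late conversion can matter. It does not measure the defect.

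**4. Error rate if success is allowed at either time.** The protocol gives no within-subject variability, so it is assumed over a range. Model: log counts with no treatment effect in any arm; a serially correlated component (correlation exp(−months/12)) plus an independent component; 20 per arm, three arms, complete data, 20,000 runs. Each active arm is compared with placebo at 0.025, and an error is a significant result in either comparison.

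| SD, correlated / independent | Response rate to M18 | Response rate to M24 | Family-wise error, M18 only | M24 only | M18 or M24 |
|---|---|---|---|---|---|
| 0.3 / 0.3 | 7.4% | 8.4% | 0.010 | 0.016 | 0.017 |
| 0.5 / 0.4 | 17.3% | 19.5% | 0.042 | 0.042 | 0.055 |
| 0.7 / 0.5 | 24.8% | 27.5% | 0.042 | 0.045 | 0.057 |
| 0.9 / 0.5 | 29.2% | 32.3% | 0.048 | 0.048 | 0.064 |

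The added window raises the chance response rate by 1.0 to 3.1 points (8.4−7.4 and 32.3−29.2). The inflation comes from having two chances, not from M24 itself. The last column assumes the extension always happens. An extension made only after a visible trend gives fewer second chances, so under this model the column is an upper limit for that rule. The simulation does not cover loss of subjects through re-consent.

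**5. Sections side by side.** Section 11.4 makes the albendazole offer conditional on completion of the study and on unblinding. The amendment's opening says the study reached its term and was unblinded, which reads as both conditions met at M18. Its consent paragraph says the trial was prolonged to 24 months, which reads as completion at M24. The document does not say which applies.

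**The case against.** The case on the other side has real force.

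- **Pooling is nowhere stated.** The amendment calls the readings supplementary, leaves sections 5.2, 7.1.1 and 9 untouched, and section 7.2 lists the efficacy evaluations as M2 to M18. A reader might infer that M21/M24 will enter the primary proportion. The documents do not say so; they only fail to exclude it. A cut-off may stand in an analysis plan not seen here. But the amendment itself changed the last visit, and section 12.10 times the report of all analyses from the last follow-up visit. The cut-off therefore belongs in the protocol text.
- **Contamination of the control arm is not shown.** A reader might infer that placebo subjects took albendazole before M21. Section 11.4 describes an offer with two conditions, and section 6.2.9 advises against albendazole outside study treatment during the study. It is possible, not established.
- **The 0.025 test is not broken.** A reader might infer that the extension invalidates it. It does not: the M0-M18 data were complete before the decision, and a test confined to them is unaffected.
- **Unblinding at M18 was not an unplanned interim look.** Section 9.2.4 says "No interim analysis is planned", and the code was opened at the planned end, so that section is not breached.
- **Safeguards exist.** Section 6.2.9 already records medication at each visit. The slide reading used for analysis is blinded to subject number, date and time (section 6.1.7.1), and the amendment keeps the same procedures. That protects the counts, but not the choice to extend or who returns.

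What stands is the missing boundary at M18 for the endpoint and the populations.

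**Conclusion.** The point holds in a limited form. The visits were added after unblinding in response to one arm's trend, and the amended protocol leaves them able to enter the primary proportion and to redefine who is analysed. The effect is one extra response window. If success were allowed at either M18 or M24, family-wise error would rise from about 0.042-0.048 to 0.055-0.064, against an intended total of 2 × 0.025 = 0.05. At very low variability it stays well below 0.05 (0.010 to 0.017). These error rates rest on assumed within-subject standard deviations and an assumed correlation pattern. That the new window exists, and that the populations are open to redefinition, follows from the text alone. The M18-only comparison remains sound, and the correction serves to keep it identifiable as the primary result.

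**What to change.** - In sections 5.2, 7.1.1 and 9.2.3 and in the amendment, state that the primary endpoint and every other tested efficacy endpoint use M2-M18 only, and that the final efficacy assessment means M18.
- Report M21 and M24 by arm as descriptive results, labelled as added after unblinding.
- Reconcile section 11.4 with the amendment's statements that the study reached its term, that the blind was lifted and that the trial was prolonged to 24 months. When the offer falls is for the sponsor and investigator to state.
- Show any albendazole taken after M18, as recorded under the existing medication question in section 6.2.9, alongside the M21/M24 results.

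The cost is a few sentences and one extra breakdown in the report. Sample size and alpha are unchanged. The downside is that M21 and M24 cannot support a confirmatory claim.
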